### Blinding

This is a pragmatic trial comparing two rehabilitation interventions. It will therefore not be possible to blind participants or their clinicians to treatment group allocation. The research assistants will collect outcome measurements blind to treatment allocation. They will not be informed to which group the patient participants have been allocated and will not be present at any of the therapy sessions. Before any home visits for follow-up assessments, they will ask participants not to reveal their treatment allocation. After the final follow-up assessment, they will complete a perception of allocation form, in order to monitor the level of blinding achieved for these researchers. Data analysis will be performed blind to treatment allocation.

### Internal pilot

An internal pilot-assessed site recruitment and participant recruitment and retention rates for the 6 months after the first site were open to recruitment from September 2019 to February 2020.

#### Progression criteria

Number of sites open: seven or more (go); five to six (amend); four or fewer (stop).Open site recruitment rate per month: two or more (go); one to two (amend); less than 1 (stop).Retention rate: 69% or higher (go); 50%–68% (amend); 49% or fewer (stop).

### Statistical analysis

Final analysis will take place once all participants have been followed up for 52 weeks, and the database has been locked. Analyses will be by ‘intention to treat’ for the primary and secondary outcomes on all randomised participants, in the group to which they were allocated and for whom the outcomes of interest have been observed or measured.

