## Introduction

Proximal femoral fracture, more commonly referred to as hip fracture, is a common, major health problem in old age.^1^ It is projected to increase further as the population ages.^2 3^ Mortality is high,^4 5^ and of those who survive to 1 year, 29% fail to regain their level of functioning, in terms of restrictions of activities of daily living^6^; many lose their independence. This imposes a large cost burden on society, estimated to be approximately £2.3 billion a year in the UK.^7^ The majority of costs is incurred in the community and social care setting in the 12 months following hospital discharge, which are almost four times higher than the costs of the acute hospital admission.^8^ Frail individuals are at particular risk of secondary future proximal femoral fracture, resulting in worse morbidity and mortality outcomes.^9^

The National Institute of Health and Clinical Excellence (NICE) have issued guidelines for the management of hip fracture.^10^ This includes the provision of a co-ordinated multidisciplinary rehabilitation programme starting in hospital during postoperative recovery and continuing in the community following discharge.^10^ Where possible such rehabilitation programmes should consider individual patient goals, facilitate a return to prefracture independence and provide patients and carers with written information to support the rehabilitation programme and long-term outcomes. The Hip Sprint audit reported that community rehabilitation services were inconsistent.^11^

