### Sample size calculation

The phase II feasibility study results^23^ informed the sample size calculation. The adjusted mean difference in the primary outcome measure (NEADL) between the intervention and control group in the feasibility trial was 3.0. Work completed by Wu *et al*^27^ has suggested that the minimum clinically significant difference is 2.4; this has been used within the sample size calculation for this phase III RCT. A two-point score in the NEADL scale would equate to an improvement in function from being independent around the home to being able to use public transport or get in and out of a car. The adjusted mean difference between the groups in NEADL in the randomised feasibility study had an SD of 5.8. In this multisite phase III RCT, a more diverse sample would be expected, so a larger SD would be expected. Parker *et al*^42^ used NEADL in a rehabilitation RCT and found an SD of 10. Based on the analysis of covariance (ANCOVA) with alpha of 5% and 90% power to detect a difference of 2.4 (SD=10, R^2^ of covariate=0.52), 352 patient participants would be required to complete the trial over both treatment groups. When considering the 79% retention rate in the feasibility study,^23^ the trial would need to recruit 446 patient participants.

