#### Missing data and withdrawals

Predictors of missing data will be investigated using regression models (including type of surgery, age, living arrangements and comorbidities) and any significant predictors will be considered for inclusion in the models. In addition, given the two assessment points at 17 and 52 weeks, we will carry out a sensitivity analysis using a joint modelling approach to check whether there is any difference in outcome (here the longitudinal outcome rather than the outcome at 17 weeks or 52 weeks alone) between the randomised arms adjusted for dropouts or missing values.

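### The primary analysis is labelled intention to treat but uses only observed outcomes, and the one named missing-data sensitivity analysis is not aimed at the 52-week difference

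*Protocol article*

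**What the plan says.** All references are to the Protocol article.

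- **Analysis set (Statistical analysis).** Primary and secondary outcomes are to be analysed by intention to treat on all randomised participants, "in the group to which they were allocated and for whom the outcomes of interest have been observed or measured".
- **Model (Analysis of effectiveness).** ANCOVA adjusted for the baseline score and the stratification factors. The primary outcome is NEADL at 52 weeks (Primary objective; Outcomes).
- **Missing data (Missing data and withdrawals).** There are two provisions. First, missingness is regressed on factors that include type of surgery, age, living arrangements and comorbidities, and "any significant predictors will be considered for inclusion in the models". Second, one sensitivity analysis uses a joint model adjusted for dropouts or missing values. Its target is given as "here the longitudinal outcome rather than the outcome at 17 weeks or 52 weeks alone".
- **Planned loss (Sample size calculation).** The trial is sized on 352 completers. "When considering the 79% retention rate in the feasibility study", the recruitment target becomes 446.
- **Data available (Table 2).** NEADL is scheduled for every patient at baseline, 17 weeks and 52 weeks.

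**The concern.** The sentence that defines the analysis set cannot be met in both halves. A patient with no 52-week NEADL is randomised but is not in the set. The second half governs, so this is an observed-case analysis under a label that readers take to mean everyone randomised.

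The label would matter less if a stated sensitivity analysis tested the same quantity. The joint model's target combines the two visits, whereas the primary question concerns week 52. If the two results differ, the reader cannot separate the influence of missing data from a treatment effect that simply differs between 17 and 52 weeks.

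The covariate provision does not close this gap. The variables it names are all measured at baseline. They can correct dropout only to the extent that they predict it, so they miss the part that depends on how well a patient has recovered by week 17. The 17-week NEADL carries that information, but it is measured after randomisation and cannot simply be added to the ANCOVA as a covariate. It has to enter through a repeated-measures model or imputation. Choosing covariates by a significance test for missingness also leaves open, until the data are seen, what the models will contain.

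Patients and clinicians are unblinded (Blinding), so dropout that follows a different pattern in each arm is plausible.

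**Working it through.** **1. Reproduce the plan's figures.** Inputs from Sample size calculation: "alpha of 5% and 90% power to detect a difference of 2.4", with "SD=10, R^2^ of covariate=0.52". The test is assumed two-sided; a one-sided test would give 286 completers.

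- Residual SD = 10 × √(1 − 0.52) = 6.93.
- Two-sample calculation for a difference of 2.4: 176 per arm, 352 in total (power 90.1%). This matches the article.
- 352 / 0.79 = 445.6, rounded up to 446. This matches.

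**2. Size of the excluded group.** 446 − 352 = 94, and 94 / 446 = 21.1%.

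**3. How far the excluded patients could move the answer.** Suppose completers show exactly 2.4 and loss is 21% in each arm. Then the effect in all randomised patients = 0.79 × 2.4 + 0.21 × (effect in the missing).

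| Assumed effect in the missing | Effect in all randomised |
|---|---|
| 2.4 | 2.40 |
| 0 | 1.90 |
| −2.4 | 1.39 |

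The completers' standard error is 6.93 × √(2/176) = 0.739, so their significance threshold is 1.96 × 0.739 = 1.45. The all-randomised effect reaches that value when the effect in the missing is (1.45 − 1.90) / 0.21, about −2.1. It reaches zero at −1.896 / 0.21, about −9.0.

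**4. Unequal loss.** Assume that missing patients are worse than observed ones by the same gap in both arms, and that baseline adjustment does not remove the gap. Then bias = (difference in loss) × gap.

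| Assumed loss by arm | Gap 5 | Gap 10 | Gap 15 |
|---|---|---|---|
| 21% v 21% | 0 | 0 | 0 |
| 18% v 24% | 0.3 | 0.6 | 0.9 |
| 16% v 26% | 0.5 | 1.0 | 1.5 |

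**5. Dropout that depends on 17-week recovery.** This was simulated under assumptions that are not in the article: 10% lost before week 17, about 21% lost overall, and later dropout depending on 17-week NEADL in one arm only. The log-odds slope was 0.5 to 1.5 per SD and the 17-to-52-week correlation 0.75 to 0.85. The baseline-to-52-week correlation is √0.52 = 0.72, from the article's R².

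- Observed-case ANCOVA: bias of about 0.2 to 0.6 points. As a share of the target, 0.2 / 2.4 = 8% and 0.6 / 2.4 = 25%. A second run over the same slopes and correlations gave 0.12 to 0.46, so the range is approximate.
- Repeated-measures estimate of the 52-week contrast using 17-week NEADL: bias near zero (about 0.02), with a standard error about 1% to 3% smaller.

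Overall loss was nearly equal between the arms here. Comparing retention rates would therefore not reveal the bias.

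**The case against.** **Observed-case ANCOVA is a common choice and the article defines it openly.** That is fair. It is also valid when missingness depends only on the covariates in the model. With equal loss and an equal gap the bias is zero, and retention at submission was 83% (Trial status), better than planned. What remains is that the label does not describe the set, and that validity rests on an assumption that the 17-week data could relax.

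**The joint model already covers this.** A reader might infer that the lost patients are wholly unprotected and that no stated analysis would react to informative dropout. The article does not support that reading. The joint model uses both visits and adjusts for dropout. Its target excludes either visit taken alone, which does not mean that week 52 is ignored. It could yield a 52-week contrast if it included an arm-by-time term. The article does not say that it will, and the target it does state is a different quantity.

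**The covariate rule is soft.** Significant predictors are only to be considered, and the article does not say that the primary model is meant. This stands, so the point is that the rule is left open, not that the primary model is certain to be data-driven.

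**Deaths.** The Introduction says "Mortality is high", and a reader might infer that the planned 21% includes deaths, or that deaths are to be handled as dropouts. The article states neither. It does not break down the 79%, and it gives no mortality rate from which to size an effect. A rule for deaths may be in the statistical analysis plan, which is not at hand, so its absence here is not a finding.

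**Conclusion.** The point holds in a limited form. The article applies an intention-to-treat label to an observed-outcome set of about 352 of 446 patients, and it aims its one named missing-data sensitivity analysis at a quantity other than the 52-week difference. That analysis gives real but partial protection. The count of 94 excluded patients follows directly from the article's own figures.

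The bias figures are conditional. About 0.2 to 0.6 points requires dropout that depends on 17-week NEADL in one arm only, at the strengths and correlations assumed. The range of 0.3 to 1.5 points requires unequal loss and missing patients 5 to 15 points worse. If loss and gap are equal in the two arms, there is no bias. The sample size is unaffected: 352 and 446 stand.

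This does not show that the planned analysis is invalid. It shows an avoidable weakness at the primary endpoint that data already scheduled for collection can reduce.

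**What to change.** Make these changes in the protocol or the statistical analysis plan before database lock:

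1. Describe the analysis set as 'as randomised, observed outcomes', and do not describe it as all randomised participants.
2. Estimate the 52-week arm contrast from a repeated-measures model of 17- and 52-week NEADL, or from ANCOVA after multiple imputation that uses 17-week NEADL. Make this the primary analysis, or at least a committed sensitivity analysis.
3. Require the joint model to report the 52-week contrast, so that it can be set directly against the primary result.
4. Use type of surgery, age, living arrangements and comorbidities as pre-specified covariates or imputation variables, without selection by significance.

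The cost is revised wording and a slightly more complex analysis. No extra patients, visits or data items are needed.

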#### Baseline

Demographic and baseline characteristics will be summarised separately using descriptive statistics for each randomised group to allow clinical assessment of whether balance was achieved between randomised groups. No statistical testing of differences between groups will be performed.

#### Analysis of effectiveness

Primary and secondary outcomes at baseline, 17 weeks’ and 52 weeks’ follow-up will be summarised for each treatment group using descriptive statistics at each time point. If normally distributed, the difference between group means (with 95% CIs) will be reported from the ANCOVA adjusted for baseline score and stratification factors.

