**Methods and analysis:**

Protocol for phase III, parallel-group, two-armed, superiority, pragmatic RCT with 1:1 allocation ratio; allocation sequence by minimisation programme with a built-in random element; secure web-based allocation concealment. The two treatments will be usual care (control) and usual care plus an enhanced rehabilitation programme (intervention). The enhanced rehabilitation will consist of a patient-held information workbook, goal setting diary and up to six additional therapy sessions. Outcome assessment and statistical analysis will be performed blind; patient and carer participants will be unblinded. Outcomes will be measured at baseline, 17 and 52 weeks’ follow-up. Primary outcome at 52 weeks will be the Nottingham Extended Activities of Daily Living scale. Secondary outcomes will measure anxiety and depression, health utility, cognitive status, hip pain intensity, falls self-efficacy, fear of falling, grip strength and physical function. Carer strain, anxiety and depression will be measured in carers. All safety events will be recorded, and serious adverse events will be assessed to determine whether they are related to the intervention and expected. Concurrent economic evaluation will be a cost-utility analysis from a health service and personal social care perspective. An embedded process evaluation will determine the mechanisms and processes that explain the implementation and impacts of the enhanced rehabilitation programme.

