### Outcomes

Patient participants will complete outcome measures at baseline, 17 and 52 weeks administered by a research assistant blinded to participant allocation. Follow-up assessments will be completed within participants’ homes (tables 1 and 2). The primary outcome will be the difference in NEADL scale^26 27^ at 52-week follow-up, between the usual rehabilitation arm and the enhanced rehabilitation arm. At baseline, the patient will be asked to recall the 4 weeks prior to hip fracture and not 4 weeks prior to completing this questionnaire. Secondary outcomes will include the Hospital Anxiety and Depression Scale (HADS),^28^ economic measures will be EuroQol, EQ-5D-3L^29^ and Client Service Receipt Inventory.^30^ A reduced version of this will be used at baseline to reduce participant burden as they recover from hip fracture surgery. Potential mediators of outcome will include a Visual Analogue Scale (VAS) for hip pain intensity,^31^ Falls Efficacy Scale—International (self-efficacy)^32 33^ and Visual Analogue Scale—Fear of Falling (VASFoF).^34^

**Table 1 T1:** Outcome measures

Patient completed measures—primary	Description	Range
Nottingham Extended Activities of Daily Living scale^26 27^	Activities of daily living (mobility, kitchen, domestic, leisure) with higher score indicating greater independence	(0–66)

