**Carer completed measure—secondary outcome**		
Caregiver Strain Index^42^	13 items in the domains: employment, financial, physical, social and time. Positive responses to seven or more items indicate a greater level of strain	(0–13)
HADS^28^	Anxiety and depression in carers. Two subscales (0–21) with higher score indicate greater anxiety or depression	(0–21)

**Table 2 T2:** Fracturein the Elderly Multidisciplinary Rehabilitation—phase III (FEMuR III) protocol schedule of forms and procedures

Procedures	Screening	Baseline/randomisation*	Trial intervention†	17 weeks postrandomisation follow-up	Qualitative interviews	52 weeks postrandomisation follow-up
Eligibility screening and consent						
Assessment of eligibility criteria	X					
Written and informed consent (patient/carer)	X					
Confirm consent		X	X	X	X	X
Randomisation		X				
Discharge data		X				
Outcome measurement— patient						
Nottingham Extended Activities of Daily Living		X		X		X
Hospital Anxiety and Depression Scale (HADS)		X		X		X
Abbreviated Mental Test Score		X		X		X
Visual Analogue Scale (VAS) hip pain intensity		X		X		X
Falls Efficacy Scale—International		X		X		X
Visual Analogue Score—Fear of Falling		X		X		X
EuroQol-5D-3L		X		X		X
Client Service Receipt Inventory		X		X		X
Grip strength		X		X		X
Short Physical Performance Battery				X		X
Outcome measurement— carer						
Caregiver Strain Index		X		X		X
HADS		X		X		X
Trial intervention†			X			
Qualitative interviews						
Re-affirm consent verbally specifically for qualitative phone interview. (patient/carer)					X	
Qualitative telephone interview					X	
Safety event reporting						
Monitoring of adverse events			X	X	X	X
Monitoring of serious adverse events			X	X	X	X

Participant follow-up visits should take place at 17 (±2 weeks) and 52 (±2 weeks) weeks postrandomisation.

*Randomisation and baseline should take place no later than 6 weeks after hip fracture repair surgery.

†If randomised to intervention arm.

The research assistant will assess patient participants’ cognitive function at baseline, 17 and 52 weeks using the Abbreviated Mental Test Score.^35^ The research assistant will measure physical function at baseline, 17 and 52 weeks using the grip strength test^36–38^ and using the Short Physical Performance Battery^39 40^ at 17 and 52 weeks.

Carer participants will complete the Caregiver Strain Index^41^ and the HADS^28^ at baseline, 17 and 52 weeks.

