#### Mediation analyses

The hypothesised mechanism of change for the enhanced rehabilitation intervention is that participants’ primary outcome (activities of daily living) is mediated by self-efficacy, hip pain, cognitive function, fear of falling and physical function. If the enhanced rehabilitation intervention has a significant effect on primary outcome (p<0.05) for enhanced rehabilitation in ANCOVA, causal mediation analysis will be used to determine whether each of these potential mediators predict change in NEADL at 52 weeks. Initial assessments will determine whether the randomised intervention affects each putative mediator in turn. For those putative mediators that are significantly (p<0.1) affected by the randomised intervention, mediation analysis will be carried out adjusting for baseline covariates that predict both the mediator and NEADL, potentially including type of surgery, age, living arrangements (alone/with others) and comorbidities. Sensitivity analyses will assess the potential impact of unmeasured confounding between the mediator and NEADL.

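### The ANCOVA adjusted for baseline score cannot be fitted to the Short Physical Performance Battery, which has no baseline; naming substitute covariates would fix this and gain precision

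*Protocol article*

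**What the plan says.** The Analysis of effectiveness section gives one rule for outcomes. First, "Primary and secondary outcomes at baseline, 17 weeks’ and 52 weeks’ follow-up will be summarised for each treatment group". Then, if the data are normally distributed, the "difference between group means (with 95% CIs) will be reported from the ANCOVA adjusted for baseline score and stratification factors". No outcome is exempted.

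The abstract counts physical function among the secondary outcomes: "Secondary outcomes will measure anxiety and depression, health utility, cognitive status, hip pain intensity, falls self-efficacy, fear of falling, grip strength and physical function". Table 1 places the SPPB, scored 0–12, beside grip strength as an objective measure of physical function.

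The text after Table 2 schedules the two measures differently. For grip strength: "The research assistant will measure physical function at baseline, 17 and 52 weeks using the grip strength test". For the SPPB, the assistant will measure function "using the Short Physical Performance Battery^39 40^ at 17 and 52 weeks". Table 2 agrees, and the SPPB is the only outcome row there without a baseline mark.

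The NEADL is also collected at baseline, for the period before the fracture: "At baseline, the patient will be asked to recall the 4 weeks prior to hip fracture". The Randomisation procedures section places baseline measurement before randomisation.

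Physical function is one of the hypothesised mediators. The Mediation analyses section plans "adjusting for baseline covariates that predict both the mediator and NEADL, potentially including type of surgery, age, living arrangements (alone/with others) and comorbidities", together with sensitivity analyses for unmeasured confounding between mediator and NEADL.

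**The concern.** The rule for secondary outcomes and the measurement schedule cannot both be followed for the SPPB. There is no baseline to summarise and no baseline score to adjust for. Someone will have to choose a replacement model: stratification factors only, grip strength, NEADL, or both. Each choice gives a somewhat different estimate and interval, so it should be fixed before the data are seen.

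The default, deleting the missing term, is also the least efficient choice. It leaves the only listed measure of lower-limb function with no prognostic functional covariate in its model, although two are already collected. The same estimate feeds the p<0.1 screen that decides whether physical function goes forward as a mediator, so precision matters there too.

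**Working it through.** **1. Setting the sections side by side.**

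| Requirement (Analysis of effectiveness) | SPPB (Table 2 and text) | Can it be done? |
|---|---|---|
| Summary at baseline, 17 and 52 weeks | 17 and 52 weeks only | Not at baseline |
| ANCOVA with the outcome's baseline score | No baseline score | No |
| ANCOVA with stratification factors | Known at randomisation | Yes |

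Grip strength and NEADL both have baseline values taken before randomisation, so either can serve as an ANCOVA covariate for the SPPB.

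**2. The plan's own figure.** The Sample size calculation section uses a difference of 2.4, SD 10, covariate R² 0.52, alpha 5% (taken as two-sided) and 90% power.

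- Adjusted SD = 10 × √(1 − 0.52) = 6.93.
- n per arm = 2 × (1.960 + 1.282)² × 6.93² / 2.4², rounded up to 176; total 352.
- Recruitment = 352 / 0.79 = 445.6, rounded up to 446.

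Both stated figures reproduce. They concern NEADL, which has a baseline, and do not change.

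**3. What a covariate is worth for the SPPB.** The documents give no SD, target difference or R² for the SPPB, so this is an illustration in SD units with 176 per arm. The confidence interval width is multiplied by √(1 − R²). The equivalent gain in sample size is 1/(1 − R²) − 1. The detectable difference at 90% power is (1.960 + 1.282) × √(2/176) × √(1 − R²). Power is shown for a difference of 0.24 SD, which is the NEADL design difference (2.4/10) borrowed as a yardstick.

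| R² (assumed) | Interval width ratio | Equivalent sample gain | Detectable difference (SD) | Power at 0.24 SD |
|---|---|---|---|---|
| 0 | 1.000 | 0% | 0.346 | 61% |
| 0.2 | 0.894 | 25% | 0.309 | 71% |
| 0.4 | 0.775 | 67% | 0.268 | 83% |
| 0.52 (the NEADL value) | 0.693 | 108% | 0.239 | 90% |

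If grip strength and pre-fracture NEADL together explain 20–40% of SPPB variance, the interval is 11–23% narrower than with no useful covariate. At an R² of 0.1 the width ratio is 0.949, a gain of about 5%.

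**4. Bias.** Allocation is randomised, so leaving out a baseline covariate does not bias the between-arm SPPB comparison. The loss is in precision.

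**The case against.** The strongest reply is that this is a condensed article, and that exceptions for single secondary measures belong in a statistical analysis plan that is not shown. That stands as far as an unnamed covariate goes: silence alone would be no finding. But the published text is not silent. It states a baseline summary and a baseline-adjusted model for secondary outcomes, and its own schedule rules both out for one of them.

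A second reply is that the ANCOVA applies only if data are normally distributed, and a score bounded at 0–12 may not qualify. That is fair, but it does not remove the baseline summary, and it gives no model for the case where the SPPB does qualify.

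A reader might infer several stronger things that the documents do not support:

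- *That the SPPB is the main physical-function outcome.* No section says so; it is listed alongside grip strength.
- *That its estimate will be less precise than that of every other outcome.* The only R² given is for NEADL, so no such ranking can be made.
- *That the mediation plan omits prior function and so inflates the mediated share.* The covariate list is open and chosen by a criterion. Baseline NEADL or grip strength qualifies if it predicts both mediator and outcome. The section also plans sensitivity analyses for unmeasured confounding, and mediation is run only if the primary result is significant.

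**Conclusion.** The point holds as a correctable inconsistency with a nearly free improvement attached. The stated baseline summary and ANCOVA cannot be carried out for the SPPB. Dropping the baseline term leaves a valid, unbiased comparison adjusted for stratification factors only, with avoidable loss of precision.

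The size of that loss is unknown from the documents. The 11–23% narrowing rests entirely on an assumed R² of 20–40% and would be smaller if grip strength and recalled NEADL predict the SPPB poorly.

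For mediation there is no error to correct. Because the SPPB lacks its own baseline, early lower-limb function can be adjusted for only by proxy, so naming the proxies would be a helpful clarification. The primary analysis and the 352/446 sample size are untouched.

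**What to change.** In the Analysis of effectiveness section, or in the statistical analysis plan if it does not already say so, add: *The SPPB is not measured at baseline and has no baseline summary. Its ANCOVA adjusts for baseline grip strength and baseline (pre-fracture) NEADL in place of its own baseline score, plus the stratification factors. Results are reported as a difference between groups at follow-up, not as a change from baseline.* The last part also settles how the Secondary objectives, which speak of change in physical function, are to be read for this measure.

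As an optional clarification, name baseline NEADL and grip strength among the candidate confounders in Mediation analyses when the SPPB is the mediator.

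The cost is a sentence or two and two degrees of freedom in a model with about 352 completers. No new data are needed. The wording should be fixed before the data are seen.
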